### Qualitative Component

Caregivers’ recognition and responses to childhood fevers and HEWs’ views and experiences of their position in the health care system during previous and, in particular, the current recommendations in the respective intervention arms will be explored using semistructured interviews at a time point when the interventions are fully adopted by the HEWs (determined based on a stable enrollment rate). A subset of mothers and HEWs in both arms will be selected for inclusion in these interviews to help put the findings into context.

### Randomization

Cluster randomization will be at the health center level, corresponding to the lowest administrative unit where HEW services are coordinated; there will be 25 clusters in the 3 study woredas, with an average of 5 health posts and 7.5 HEWs per cluster. All clusters will be eligible for randomization. Restricted randomization will be performed to minimize the difference between intervention and control arms on key indicators, including average under-five population size, cluster distance to nearest zonal referral hospital, and number of unclassified fevers in children under 5 years seen by HEWs [23]. A validity matrix will be produced to confirm that no pairs are more or less likely to appear together than they would by chance. Sorting of clusters and random selection of schemes will be carried out in STATA 13 (STATA Corp, College Station, TX, USA).

### Sample Size

The primary outcome on which sample size is based is the percentage of children with persistent fever, illness, or decline (hospital, danger signs develop, or death) at day 8. It is assumed that about 5% of children in both groups will still be ill at day 8 (based on rates of ~3% and 8% in previous studies [16,24]) and that this percentage will be approximately equivalent between groups. To calculate sample size, the outcome rate (ill at day 8) in the universal follow-up group is set to 5%, and it is assumed that the (true) corresponding outcome percentage in the conditional follow-up group will be no more than 6%. For the purpose of concluding that the conditional follow-up is noninferior to the universal follow-up approach, the upper bound of a one-sided 95% CI around the absolute difference in outcome rate (conditional minus universal) must not exceed 4% (noninferiority margin), assuming a power of 80% and an alpha of 5%. A design effect of 3 is used to account for clustering at HEW and health facility levels, generating a total sample size of 4284 children, with 2142 in each arm. To compensate for 10% loss to follow-up at day 8 and an additional 5% loss between day 8 and day 15, a total of 4900 children will be enrolled. Enrollment will occur over a period of 1 year to account for seasonality of various causes of febrile illness, starting in December 2015 and is expected to be completed around December 2016.

### Outcomes

All enrolled children will have a study visit in their home with an IE after 1 week to assess their clinical outcome. Children who have not recovered on day 8 will be re-assessed after 2 weeks, and those whose illness persists on day 15 will be re-assessed on day 29. In addition, all enrolled children will be followed-up via a phone call for vital status on day 28. Management of illness at any follow-up visit (ie, return to HEW on any day; return to HEW for universal day 3 visit; or day 8, 15, and 29 assessment) will follow established national IMNCI guidelines.

The primary outcome is treatment failure on day 8, defined as the proportion of children with unclassified fever who subsequently declined clinically (death, hospitalization, one or more danger signs or persistent fever).

Secondary outcomes include:

Clinical presentation in those with unresolved illness at day 8 in each armTreatment failure on day 15 and 29, defined as the proportion of children with unclassified fever who subsequently declined clinically (death, hospitalization, one or more danger signs or persistent fever)Percentage of children who present to the HEW for the follow-up visit on day 3 in the universal follow-up armPercentage of children who spontaneously represent to HEW for persistence or worsening of symptoms in the conditional follow-up arm, and the timing of these visitsPercentage of children receiving secondary treatment (antimicrobial medicines prescribed during visits to any providers after initial presentation to HEW) in each arm between enrollment and day 8Caregiver and HEW acceptability of universal and conditional follow-up recommendations

### Data Collection

HEWs will collect data using an Open Data Kit (ODK) [25] data collection form on mobile phones. Data will include date of enrollment, child identifiers, and clinical indicators (fever/axillary temperature, cough, respiratory rate, diarrhea, and danger signs). The enrollment data will be synchronized with a server which is accessed by a data manager who will download enrollments on a daily basis and schedule follow-up visits for 6 IEs using an online Google calendar.

The IEs will be equipped with tablets programmed with 3 ODK data collection forms; one for the day 8 visit, one for any extra visits (on day 15 or 29), and one vital status form for day 29. The data that will be collected during the household follow-up visits on day 8, 15, and 29 will include clinical data for the children following the IMNCI algorithm (eg, fever/axillary temperature, cough, respiratory rate, diarrhea, mid-upper arm circumference (MUAC) measure, and danger signs), any secondary treatment (antimicrobial medicines prescribed during visits to any providers after initial presentation to HEWs), hospitalization, care-seeking history, and costs, as well as caregiver and household characteristics. For children who cannot be found at home at the time of the home visit, 2 more attempts will be made over the 2 following days. After this, the child will be registered as a loss-to-follow-up for the primary outcome.

Moreover, 3 research assistants will enter data collected by HEWs for children who come back to the HEW spontaneously (universal and conditional arm) or on day 3 (universal arm) into an ODK sick child assessment form every 2 weeks.

A rigorous monitoring system will be implemented by the study team and will be part of the continuous quality assurance. The data manager will review forms submitted to the server daily and check for duplicates, completeness, and accuracy before storing them in the project database. Discrepancies, overdue follow-up visits, and other issues will be resolved by phone calls to the IEs and during weekly supervision meetings with field research staff. Biweekly field supervision visits to all HEWs will be carried out, and district HEW supervisors will be trained to monitor HEW trial activities during routine weekly group supervisions. A minimum of 10% of all enrolled cases and 50% of children with treatment failure will have a quality control re-assessment by a research assistant. The final dataset will be exported to STATA 13.

Semistructured interviews with HEWs and caregivers of children enrolled in the study will be conducted when a stable enrollment rate has been established in the study (assumed to be after 3 months). HEW interviews focus on what decentralization of health care mean to HEWs, how changes in follow-up recommendations are perceived, how they describe their roles in the communities, and how health system changes affect this role and their work situation. Caregiver interviews will aim to improve the understanding of caregiver perceptions of childhood illnesses, their perceived causes, and treatment options in the 3 woredas. Interview guides will capture how caregivers (assume primarily mothers) of sick children experience illness episodes and treatment seeking inside and outside the household. Focus will be on how caregivers describe the illness episode from the beginning to the recovery, current health status, actions that are taken or not taken when a young child gets fever, who is involved in the care of the child, and what their perceptions and experiences are with the recommended follow-up action they have been exposed to when visiting the HEW. Half of the HEWs and mothers to be interviewed will be from the study arm using the universal follow-up advice and the other half will follow the conditional follow-up recommendation. HEWs will be purposively selected, based on who has enrolled the highest number of children for the cRCT. Mothers of children enrolled in the study in the 2 weeks preceding the start of the qualitative data collection will be included using simple random sampling. A minimum of 1 week should have passed since the day 8 visit was completed to avoid study fatigue.

Interview guides will be separately prepared for the HEW and caregiver interview and translated into Amharic. In addition, 2 male, Amharic-speaking interviewers will conduct the HEW interviews and 1 additional male Amharic interviewer will be recruited for the caregiver interviews.

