### Data Analyses

The analysis of the primary outcome, treatment failure on day 8, will be done following a per-protocol approach. The baseline characteristics of the children and caregivers in both arms will be summarized using descriptive statistics. The difference between the percentage of the main study outcomes (persistent fever, persistent illness, or clinical deterioration [mortality, hospitalization, or danger signs], and these outcomes combined) of the 2 follow-up arms will be calculated. If the upper bound of the 95% CI of the difference in this percentage is less than 4%, the null hypothesis will be rejected; the conclusion will be that the conditional follow-up approach is not inferior to the standard approach. If there are imbalances in baseline characteristics across the 2 intervention arms, adjusted analyses of the difference in percentages will be conducted using multivariate logistic regression models.

The primary outcome will be compared between groups using generalized linear models with a binomial distribution and identity link using a robust variance estimator, treating cluster as a random effect. We will apply a conventional statistical noninferiority test using a CI approach using the exact binomial CI for the difference in overall treatment failure between intervention arms. The main analysis will be done using the per-protocol population (only including children for whom the primary outcome was collected on day 8±1 and whose caregiver reported receiving follow-up advice from the HEW that was aligned with the study arm), as is appropriate for noninferiority and equivalence studies, together with sensitivity analysis in the per-protocol and intention-to-treat populations [26]. Other descriptive statistics, such as cost of care seeking and compliance with the intervention protocol, will be compared between study arms using *t test* and chi-square statistics, respectively.

Qualitative interview transcripts from HEWs and caregivers will be coded and merged into sub-categories, categories, and themes using Nvivo (NVivo qualitative data analysis Software; QSR International Pty Ltd. Version 11, 2015). HEW interviews will be analyzed first and its results reviewed after caregiver interviews are read. For the purpose of this study, caregiver interviews will be analyzed and compared with main themes identified in the HEW interviews.

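### The loss-to-follow-up rule makes no exception for death or hospitalization, and the last permitted attempt (day 10) falls outside the day 8±1 primary set, so failures may be lost more often than non-failures

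*Protocol article*

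**What the plan says.** The Outcomes section defines failure as the proportion of children who "subsequently declined clinically (death, hospitalization, one or more danger signs or persistent fever" by day 8, and ties its measurement to one contact: "All enrolled children will have a study visit in their home with an IE after 1 week to assess their clinical outcome".

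For a child not found at home, Data Collection provides that "2 more attempts will be made over the 2 following days", and then: "After this, the child will be registered as a loss-to-follow-up for the primary outcome".

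Data Analyses restricts the main per-protocol population, among other conditions, by "only including children for whom the primary outcome was collected on day 8±1". The same sentence adds other populations: "together with sensitivity analysis in the per-protocol and intention-to-treat populations".

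Two further sources of information exist. Outcomes states that "all enrolled children will be followed-up via a phone call for vital status on day 28". Hospitalization is among the items in "The data that will be collected during the household follow-up visits on day 8, 15, and 29". Home visits after day 8 are planned for children who had not recovered by day 8.

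**The concern.** Whether a child counts as lost depends on where the child is, and that can depend on the outcome. A child in hospital from day 8 to day 10 is not at home, and the caregiver may be away too. Read literally, the rule gives such a child no primary outcome, although hospitalization is itself a failure. A child who died by day 8, and whose family was not reached, is in the same position even if the later call reveals the death.

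Separately, two written rules do not fit together: Data Collection permits an attempt whose result Data Analyses excludes from the primary set.

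This is the safety endpoint of a noninferiority trial. If failures go missing more often than non-failures, to a similar degree in both arms, both observed rates fall and a true difference shrinks. The trial then becomes more likely to declare noninferiority when the conditional arm is in fact worse by the margin.

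**Working it through.** **Inputs from the Sample Size section.** Failure 5% (universal) and 6% (conditional); margin 4 points; one-sided alpha 5%; power 80%; design effect 3; 2142 per arm; 10% loss at day 8; 4900 enrolled, or 2450 per arm if split equally.

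**1. The plan's own figure.** n per arm = (1.645 + 0.842)² × (0.05×0.95 + 0.06×0.94) / (0.04 − 0.01)² = 713.7, rounded up to 714. Times the design effect of 3 gives 2142 per arm, 4284 in total. This matches the stated sample size, which the present point does not affect. The same variance approach is used below.

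**2. The calendar.** First visit on day 8, further attempts on days 9 and 10. The window 8±1 covers days 7, 8 and 9. The day 10 attempt falls outside. It would fall inside only if first visits were made on day 7, but the visit is scheduled for day 8.

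**3. What happens to each kind of child under the written rules.**
- Family at home and reports an admission or death: the text does not say how this is coded. Because the visit records hospitalization, counting it as failure is the natural reading.
- Child admitted over days 8 to 10 and nobody reached: lost. No later home visit is stated for a child never assessed on day 8, and the phone call covers vital status only.
- Death by day 8, family not reached, death learned from the later call: lost for the primary outcome. The text does not link the call to the day 8 outcome.
- Child found on day 10: outcome collected and outside the primary set, but available to the intention-to-treat analysis.

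**4. Illustration of size (the loss rates are assumptions, not in the protocol).** True rates are exactly at the margin, 5% vs 9%. In both arms 10% of non-failures and a fraction s of failures are missing.

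Observed rate = p(1−s) / [p(1−s) + (1−p)×0.9].

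For s = 0.20:
- universal: 0.040 / (0.040 + 0.855) = 4.47%, on 2450 × 0.895 = 2193 children
- conditional: 0.072 / (0.072 + 0.819) = 8.08%, on 2450 × 0.891 = 2183 children
- difference 3.61 points
- SE = √[3 × (0.0447×0.9553/2193 + 0.0808×0.9192/2183)] = 1.27 points
- one-sided error = Φ[(4 − 3.61)/1.27 − 1.645] = about 9%

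| Failures missing | Observed rates | Difference (points) | One-sided error |
|---|---|---|---|
| 10% (not selective) | 5.00% vs 9.00% | 4.00 | 5.0% |
| 20% | 4.47% vs 8.08% | 3.61 | about 9% |
| 30% | 3.93% vs 7.14% | 3.21 | about 16% |
| 50% | 2.84% vs 5.21% | 2.37 | about 47% |

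In the 20% row total loss is 10.5% and 10.9%, close to the planned 10%. The planned loss rate alone would not reveal the problem.

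**5. How extreme the loss would have to be to hide the whole margin.** Suppose found children fail at 5% in both arms, 10% are lost, and lost universal-arm children also fail at 5%. The true difference reaches 4 points only if 0.10 × (f − 0.05) = 0.04, so f = 45% of lost conditional-arm children would have to be failures.

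**The case against.** A reader might infer that dead and hospitalized children are recorded as lost and that failures are therefore selectively removed. The text does not say so. The rule covers children who cannot be found at home, a caregiver who is found can report either event, and children may be absent because they are well. Selective loss is a risk, not a demonstrated effect.

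Day 10 outcomes are not discarded altogether, since nothing bars them from the intention-to-treat analysis. Nor are children found on day 10 shown to fail more often. A child found at home that day is neither dead nor currently admitted, so the window mismatch does not in itself remove the gravest events. A per-protocol window narrower than the contact schedule can also be a deliberate choice.

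A larger figure is tempting. If 22 dead or admitted children, about 1% of an arm, were logged as lost in the conditional arm only, the rate with them restored would be (0.06×2205 + 22)/2227 = 6.93% instead of 6.00%. With the truth at the margin and an SE of 1.35 points, the one-sided error would be Φ(0.93/1.35 − 1.645) = about 17%. That needs 1% serious events lost, none in the other arm, and the truth at the margin. The protocol supports none of these and gives no admission rate. Its national under-five mortality of 58 per 1000, spread evenly over about 260 weeks, is 0.02% per week, or about half a death per 2450 children. That is a crude guide, because febrile children are not average children.

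Finally, this is a condensed article, and the handling of missing outcomes is commonly left to the analysis plan. Its absence here is no finding. What stands is what is written: a loss rule for the primary outcome without an exception for two of that outcome's components, and an attempt schedule that runs past the primary window.

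**Conclusion.** The point holds as a gap between stated rules. Followed literally, they drop from the primary analysis any child admitted over days 8 to 10 and not reached, any death by day 8 learned only later, and any outcome collected on day 10. Loss can therefore depend on the outcome.

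Similar selective loss in both arms favors noninferiority when the conditional arm is truly worse. Unequal loss could push either way, and loss unrelated to outcome causes no bias. The size cannot be derived from the protocol. The figure of about 9% instead of 5% rests on assumed missingness of 20% of failures and 10% of non-failures, true rates of 5% and 9%, and a design effect of 3. Hiding the full margin would take an extreme failure rate among the lost. The protocol does not show that failures are in fact removed, or that a 17% error is to be expected.

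**What to change.** 1. State that any death or hospitalization known to have occurred by day 8 counts as treatment failure, whatever the source or date of the information: relatives or neighbours at any attempt, HEW records, or the day 28 vital-status call. Class as lost for the primary outcome only children with no such information.
2. Align the per-protocol window with the attempts (days 7 to 10), or keep ±1 and report the day 7 to 10 set as a sensitivity analysis.
3. Report the number lost by arm, and vary the assumed failure rate among them, as in the last step of the working.

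The cost is analysis wording and a review of records already held. Widening the window adds one day of spread to the fever assessment. One limit remains: with enrollment complete and the call restricted to vital status, admissions among children never contacted may stay unknown.

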### Data Analyses

The analysis of the primary outcome, treatment failure on day 8, will be done following a per-protocol approach. The baseline characteristics of the children and caregivers in both arms will be summarized using descriptive statistics. The difference between the percentage of the main study outcomes (persistent fever, persistent illness, or clinical deterioration [mortality, hospitalization, or danger signs], and these outcomes combined) of the 2 follow-up arms will be calculated. If the upper bound of the 95% CI of the difference in this percentage is less than 4%, the null hypothesis will be rejected; the conclusion will be that the conditional follow-up approach is not inferior to the standard approach. If there are imbalances in baseline characteristics across the 2 intervention arms, adjusted analyses of the difference in percentages will be conducted using multivariate logistic regression models.

The primary outcome will be compared between groups using generalized linear models with a binomial distribution and identity link using a robust variance estimator, treating cluster as a random effect. We will apply a conventional statistical noninferiority test using a CI approach using the exact binomial CI for the difference in overall treatment failure between intervention arms. The main analysis will be done using the per-protocol population (only including children for whom the primary outcome was collected on day 8±1 and whose caregiver reported receiving follow-up advice from the HEW that was aligned with the study arm), as is appropriate for noninferiority and equivalence studies, together with sensitivity analysis in the per-protocol and intention-to-treat populations [26]. Other descriptive statistics, such as cost of care seeking and compliance with the intervention protocol, will be compared between study arms using *t test* and chi-square statistics, respectively.

Qualitative interview transcripts from HEWs and caregivers will be coded and merged into sub-categories, categories, and themes using Nvivo (NVivo qualitative data analysis Software; QSR International Pty Ltd. Version 11, 2015). HEW interviews will be analyzed first and its results reviewed after caregiver interviews are read. For the purpose of this study, caregiver interviews will be analyzed and compared with main themes identified in the HEW interviews.

Interim data analysis reports are produced on a quarterly basis to document cluster-specific cumulative enrollment rates, adherence to follow-up recommendations, and characteristics of the children and households enrolled. Deviance from the study protocol, or in expected enrollment rates, is acted on by providing refresher training and supervision to HEWs and research staff.

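### Covariate adjustment depends on observed baseline imbalance, with no criterion, and uses a logistic model with no stated route to the risk difference on which noninferiority is judged

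*Protocol article*

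**What the plan says.** The Data Analyses section makes adjustment conditional: "If there are imbalances in baseline characteristics across the 2 intervention arms", then "adjusted analyses of the difference in percentages will be conducted using multivariate logistic regression models". It gives no threshold for imbalance and no list of characteristics to check.

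The margin is on the absolute scale. In the Sample Size section the upper limit of a one-sided 95% interval "around the absolute difference in outcome rate (conditional minus universal) must not exceed 4% (noninferiority margin"). The decision rule in Data Analyses uses the same scale. The model named there for the primary comparison is binomial with an identity link, a robust variance and a random effect for cluster.

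The Randomization section says "Restricted randomization will be performed to minimize the difference between intervention and control arms on key indicators". It names three: the size of the under-five population, distance to the referral hospital, and the number of unclassified fevers seen. The list is introduced as non-exhaustive. Neither section says that these variables enter any analysis.

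**The concern.** Three features of the adjusted analysis are poorly fixed.

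- **Trigger.** Whether an adjusted result exists, and on which covariates, is settled after looking at the data and without a rule. Imbalance is not a remote possibility. The health extension workers enrol children and counsel them according to their cluster's arm, and only the day 8 evaluator is described as blinded. The per-protocol population is also selected after allocation.
- **Scale.** The stated target is a difference in percentages, but the direct output of the named model is a log odds ratio. The step between them, and the confidence limit after it, are not described.
- **Restriction variables.** Restriction exists to balance these variables, so a rule that adjusts only for what is unbalanced will tend to pass them over. With 25 clusters, that may give up precision.

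At stake is whether the adjusted result can be read against 4 points as a check on the main result, and whether available power is used.

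**Working it through.** **1. The plan's own figure.** Inputs from Sample Size: 5% (universal), 6% (conditional), margin 4 points, one-sided 5%, power 80%, design effect 3.

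n per arm = (1.645 + 0.842)² × (0.05×0.95 + 0.06×0.94) / (0.04 − 0.01)² = 6.183 × 0.1039 / 0.0009 ≈ 714.

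714 × 3 = 2142 per arm, and 2142 × 2 = 4284. The stated size reproduces exactly, and nothing below changes it.

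**2. Scale.** For control rate p, the odds ratio equal to a 4-point excess is [(p+0.04)/(1−p−0.04)] / [p/(1−p)]. The 3% and 8% are the protocol's own range ("based on rates of ~3% and 8% in previous studies").

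| Control rate | Odds ratio equal to +4 points | Excess implied by a fixed odds ratio of 1.88 |
|---|---|---|
| 3% | (0.07/0.93)/(0.03/0.97) = 2.43 | 2.5 points |
| 5% | (0.09/0.91)/(0.05/0.95) = 1.88 | 4.0 points |
| 8% | (0.12/0.88)/(0.08/0.92) = 1.57 | 6.0 points |

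An odds ratio therefore cannot be read against the margin without a baseline rate. The conversion is nevertheless available. In one simulated logistic fit with N = 4284, the adjusted odds ratio was 1.09 and averaging predicted risks under each arm gave a difference of 0.45 points. Its one-sided 95% upper limit was 1.60 points, ignoring clustering. A cluster-adjusted limit would need a further step.

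**3. Restriction variables.** An illustrative cluster-level simulation used 25 clusters (13 and 12, from Study Design) of 4284/25 ≈ 171 children. The intracluster correlation implied by the design effect is (3 − 1)/(171.36 − 1) = 0.0117. There was one restriction covariate, with allocations accepted only if the arm means differed by less than 0.15 SD. Cluster proportions were analysed by linear regression with a t-based one-sided 95% limit, in 4000 runs. The share of between-cluster variance that the covariate explains is not in the documents, so a range is shown.

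| Share explained | Type I error at the margin, unadjusted | Adjusted | Power at 5% v 6%, unadjusted | Adjusted |
|---|---|---|---|---|
| 0% | 0.056 | 0.057 | 0.788 | 0.786 |
| 30% | 0.034 | 0.046 | 0.805 | 0.852 |
| 60% | 0.020 | 0.047 | 0.821 | 0.931 |
| 90% | 0.007 | 0.052 | 0.866 | 0.985 |

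Simulation error is about √(0.05×0.95/4000) = 0.003 for the error rates and √(0.8×0.2/4000) = 0.006 for power. Ignoring the covariate lowers the type I error below 5% as the explained share rises. It never raises it beyond simulation noise.

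**4. Trigger.** No calculation was attempted, because without a criterion there is no rule to simulate.

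**The case against.** The strongest reply is that little here is an error. The article names the difference in percentages as its target and mentions no odds ratio. It condenses a fuller protocol, and covariate lists and conversion steps usually sit in an analysis plan that is not shown. The noninferiority rule is attached to the difference between arms, and the adjusted analysis is not named as its basis. Unadjusted power stays between 0.79 and 0.87, close to or above the planned 80%.

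Much of this stands, and it rules out four stronger readings that a reader might infer:

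- *That an odds ratio will be set against 4 points, so the adjusted result can never bear on noninferiority.* The text does not say this, and marginal standardization yields the difference.
- *That the restriction variables are excluded.* No covariates are named for any model, so they are neither included nor excluded.
- *That the logistic model ignores clustering.* It is not stated for that model, but the next paragraph handles clustering for the primary comparison and nothing says it is dropped.
- *That leaving out the restriction variables favours a noninferiority claim.* The simulation shows the reverse.

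The reply does not dispose of the trigger, which is a rule the article states, or of the change of scale within one section whose primary model is already on the right scale.

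**Conclusion.** The point holds in a limited form. Adjustment is tied to observed imbalance with no criterion. It is assigned to a logistic model with no described route to the adjusted difference and its cluster-adjusted limit. Both are worth correcting, but neither overturns the design, because the adjusted analysis is not the stated basis for the conclusion.

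The size of the scale problem is definite: the equivalent odds ratio runs from 2.43 to 1.57 over the protocol's own 3% to 8% range. The size of the precision loss is uncertain. At 5% v 6% the power gain from adjusting is nil if the restriction variables explain no between-cluster variance, about 5 percentage points at 30% and 11 at 60%. These gains assume one covariate, a normal cluster-level model and the correlation implied by a design effect of 3. The documents give no size for any imbalance from recruitment by staff who know the arm.

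**What to change.** - Remove the condition on imbalance. Pre-specify one adjusted risk difference that is always reported and read against the 4-point margin.
- Obtain it preferably by marginal standardization after a logistic model. A covariate-adjusted binomial model with an identity link is the alternative, but it may fail to converge at rates near 5%.
- State how its confidence interval accounts for the 25 clusters.
- Adjust for the variables that restricted the randomization, plus child covariates collected at enrolment and named in advance, such as temperature.
- The article reports enrolment complete and analysis under way, so record the choice before adjusted results are seen, or state that it was made afterwards.

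**Cost.** Wording and a little more analysis work. The cluster-level variables are already held for the randomization. Three of them use three degrees of freedom: 25 − 2 = 23 falls to 20. The sample size stays at 4284. Adjustment does not by itself remove selection by recruiters who know the arm.

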### Study Design

This is a 2-arm cluster randomized controlled trial (cRCT) carried out in 3 woredas in SNNPR in Ethiopia. Clusters defined by the health center (the lowest administrative unit where HEW services are coordinated) are randomized into either the *conditional* or *universal* follow-up arm. All children seeking care from the HEW health posts in these clusters are potential recipients of the interventions, in addition to having access to routine care available from private and public health services. Caregivers of children who meet the inclusion criteria (fever without malaria, pneumonia, diarrhea, or other symptoms requiring referral) are counseled to follow 1 of the 2 pathways, based on which intervention cluster the HEW belongs to. There are 25 clusters; 13 clusters in the universal follow-up arm and 12 in the conditional follow-up arm.

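### Two incompatible intervals are named for the primary comparison, and the one given to the noninferiority test, an exact binomial CI, ignores clustering

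*Protocol article*

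**What the plan says.** The design is clustered. Under Randomization: "Cluster randomization will be at the health center level". Under Study Design: "There are 25 clusters; 13 clusters in the universal follow-up arm and 12 in the conditional follow-up arm". The Sample Size section allows for this: "A design effect of 3 is used to account for clustering at HEW and health facility levels". It requires the upper bound of a one-sided 95% CI for conditional minus universal not to exceed 4%.

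The Data Analyses section then makes three statements about the same outcome:

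- The decision rule: noninferiority is concluded if the upper limit of the 95% CI for the difference is below 4%. It names no method for the interval and does not repeat that the interval is one-sided.
- The comparison of arms uses "generalized linear models with a binomial distribution and identity link using a robust variance estimator, treating cluster as a random effect".
- The next sentence specifies the noninferiority test as a conventional CI approach, "using the exact binomial CI for the difference in overall treatment failure between intervention arms".

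The section later says that other descriptive statistics, "such as cost of care seeking and compliance with the intervention protocol, will be compared between study arms using" t tests and chi-square statistics.

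**The concern.** An exact binomial CI for a difference in proportions takes its width from the number of children alone and has no term for correlation within health centers. The model in the preceding sentence does have one. The two will generally give different upper limits for the same difference, and the text does not reconcile them. Read in order, it attaches the noninferiority test to the interval that does not fit the design.

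The direction of the error matters. Too narrow an interval makes it easier to conclude that conditional follow-up is noninferior on an endpoint that includes death, hospitalization and danger signs, in a trial meant to inform guidelines. Leaving two intervals available also lets the choice be made after the results are seen.

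**Working it through.** **Inputs from the article.** 5% failure (universal), 6% (conditional), margin 4 points, one-sided alpha 5%, power 80%, design effect (DE) 3, 2142 per arm and 4284 in total (Sample Size); 13 and 12 clusters (Study Design).

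**1. Reproduce the sample size.** n per arm before clustering = (z(0.95) + z(0.80))² × [0.05×0.95 + 0.06×0.94] / (0.04 − 0.01)² = (1.645 + 0.842)² × 0.1039 / 0.0009 = 713.7, so 714. Then 714 × 3 = 2142 per arm, 4284 in total, an exact match. With a two-sided 95% CI the result would be 907 × 3 × 2 = 5442, which does not match. The design therefore rests on a one-sided 5% test and a variance three times binomial.

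**2. Width of the two intervals at 5% versus 6%.**
- Binomial SE = √(0.1039 / 2142) = 0.696 points; one-sided half-width 1.645 × 0.696 = 1.15 points.
- With DE 3: SE = 0.696 × √3 = 1.206 points; half-width 1.98 points.

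**3. False noninferiority rate at the margin if the binomial interval decides.** At a true difference of 4 points, the estimate has standard deviation √DE times the binomial SE, so the rate is Φ(−z/√DE).

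| True DE | One-sided 95% bound (nominal 5%) | Two-sided 95% CI (nominal 2.5%) |
|---|---|---|
| 1.5 | 9.0% | 5.5% |
| 2 | 12.2% | 8.3% |
| 3 | 17.1% | 12.9% |
| 4 | 20.5% | 16.4% |

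Only DE 3 is the article's figure; the other rows are assumptions that show the range.

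**4. Simulation.** Mean cluster size is 4284/25 = 171.4, so DE 3 implies an intracluster correlation of (3 − 1)/(171.4 − 1) = 0.0117. Beta-binomial data, 13 versus 12 equal clusters, 5% versus 9%, 200,000 runs, nominal one-sided 5%:
- unadjusted binomial (Wald) interval: 17.4%;
- the same with a continuity correction, as a proxy for the conservatism of an exact interval: 16.6%;
- cluster-level t interval on 25 − 2 = 23 df: 5.4%.

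**5. Power when clustering is respected.** With a normal reference: Φ(3/1.206 − 1.645) = Φ(0.842) = 80.0%. With a cluster-level t interval on 23 df and equal clusters, simulation gives about 78%. With unequal clusters (assumed coefficients of variation, same intracluster correlation) it gives about 76 to 77% at 0.4 and 67% at 0.8. The article gives no coefficient of variation.

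**The case against.** The strongest reply is that clustering is planned for this very outcome. The sentence just before the exact CI names a binomial identity-link model with a robust variance and a cluster random effect, and the 4% rule itself names no method. The exact-CI phrase could be a loose description of how the model's risk difference is tested. This has some force. A reader might infer that the plan ignores clustering altogether, and the text does not support that. But the sentence names a specific interval, assigns it to the noninferiority test, and does not refer back to the model, so the conflict stands.

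A reader might also take 17% as the trial's actual error rate. It is not. It needs the exact interval to decide, a true difference of exactly 4 points and a true design effect of 3, which is a planning value. An exact interval is also slightly conservative. The 5% benchmark comes from the Sample Size section, since the decision rule does not state sidedness. Rates near 21% arise only if cluster sizes are assumed to vary strongly, which pushes the design effect above 3.

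Two further inferences go too far. The article does not say that the robust variance lacks a small-sample correction, and that detail is commonly left to the analysis plan. The t and chi-square comparisons of cost and compliance are labelled descriptive and do not bear on noninferiority; the design effect of 3 is stated for the primary outcome, not for those variables.

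**Conclusion.** The point holds as a conflict between two stated methods, with the noninferiority test assigned to the one that is invalid for a cluster-randomized design. It is not a detail left to an analysis plan: the article states the method, and a plan that followed it would carry the error forward.

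Conditional on the exact binomial interval being compared with 4% and on the article's own design effect of 3, the false noninferiority rate at the margin is about 17% instead of 5% (12.9% instead of 2.5% if the CI is two-sided). The rate exceeds nominal for any design effect clearly above 1. If the cluster-adjusted interval is used, the excess largely goes. The primary conclusion therefore depends on which sentence is followed, and this should be settled before the result is reported.

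**What to change.** State one interval for the 4% rule: the one-sided 95% upper bound, as in the Sample Size section, of the risk difference from the cluster-adjusted identity-link model, preferably with a t reference on 23 df because there are only 25 clusters. A cluster-level t interval on 23 df is an acceptable alternative if it is named in advance. Delete the exact binomial CI, or keep it labelled as descriptive and outside the decision. Repeat the sidedness in the decision rule.

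The cost is wording only; no data collection changes. The interval widens to about what the sample size already budgeted. With the cluster-level t interval, power is about 78% rather than 80% for equal cluster sizes and falls further as sizes vary (step 5), so the realized variation in cluster size should be reported.

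As a secondary matter, any between-arm tests of cost and compliance should also allow for clustering, or be dropped in favor of plain description.
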